## Abstract

**Background:**

Colorectal cancer remains a considerable challenge in healthcare nowadays. Most patients’ disease develops via the adenoma–carcinoma sequence; colonoscopy with polypectomy effectively reduces both mortality and incidence by removing precancerous adenomas. Previous studies showed that polypectomy without electrocautery (cold snaring polypectomy) is a safe and time-saving procedure to manage polyps < 10 mm. However, randomized controlled trials have failed to prove the superiority of cold snaring polypectomy for reducing the risk of delayed bleeding in comparison with hot snaring polypectomy, generally because of their low statistical power that was limited by sample sizes. In this study, we aim to compare the risk of delayed bleeding following cold and hot snaring polypectomy based on a large sample size.

**Methods:**

This is a prospective multicentre randomized controlled trial to compare cold and hot snaring polypectomy for the treatment of small colorectal polyps. A total of 4258 patients with small polyps (4–10 mm) will be randomized 1:1 to each group. Colonoscopy and polypectomy will be performed by 17 experienced endoscopists at six study sites. The randomization will be performed via an online website. Pathological examination using image-enhanced endoscopy with either narrow-band imaging or chromoendoscopy will be conducted to confirm optically and histologically that complete resections have been achieved, respectively. The primary outcome measurement is the risk of delayed bleeding. The secondary outcome measurements include the number of hemoclip applications, complete eradication confirmed optically and histologically, tissue retrieval rate, procedure time, emergency unit visits, and any adverse events such as immediate bleeding or perforation.

**Discussion:**

We hypothesize that cold snaring polypectomy can reduce the risk of delayed bleeding by avoiding thermal injury. In addition, this study will also compare cold and hot snaring polypectomy in terms of the complete eradication rate and procedure time. Based on data collected, we will demonstrate that cold snaring polypectomy is a safe, effective, and economic procedure for small colorectal polyps. The results will also provide additional data on which to develop recommendations for treating small colorectal polyps.

**Trial registration:**

ClinicalTrials.gov, NCT03373136. Registered on 29 November 2017.

**Electronic supplementary material:**

The online version of this article (10.1186/s13063-018-2743-z) contains supplementary material, which is available to authorized users.

## Background

Colorectal cancer (CRC) is the third most common cancer and is the fourth leading cause of cancer-related deaths worldwide [1]. The incidence of CRC has gradually increased worldwide, except in the United States [2], where the incidence rates have declined by about 3% per year among adults aged ≥ 50 years [3]. This trend primarily reflects the effects of wider CRC screening and removal of precancerous adenomas [4]. Moreover, the decreasing mortality associated with CRC has also been observed in many countries worldwide and probably can be attributed to the expansion of CRC screening, patients’ lifestyle modifications to reduce their risk factors, and advances in treatments [4, 5].

Colonoscopy is an important modality for screening CRC and polypectomy has been proven to significantly reduce the risks of CRC incidence and associated mortality [6–8]. Polypectomy is a safe procedure, but polypectomy-related complications such as bleeding and perforation do exist [9, 10]. Nearly 80% of screening-detected polyps are < 10 mm; therefore, an important issue regards how to manage these small polyps effectively, economically, and safely. Physicians have several ways of removing small polyps, including forceps biopsy and snare polypectomy. Both forceps biopsy and snare polypectomy can be further divided into hot and cold procedures that use electrocautery or manual manipulations, respectively [11]. Snare polypectomy without electrocautery, cold snaring polypectomy, was first described more than two decades ago and has been reported to be safe and effective [12–15]. Furthermore, previous studies also disclosed that cold snaring polypectomy can save more procedural time than hot snaring polypectomy [16–19].

Cold snaring polypectomy has been considered useful for reducing the risk of delayed bleeding because it avoids electrocautery-associated thermal injury. Nevertheless, previous studies have failed to demonstrate the superiority of cold snaring polypectomy compared with hot snaring polypectomy in terms of the risk of delayed bleeding. One meta-analysis included five randomized controlled trials (RCTs) that included 668 participants and disclosed that cold snaring polypectomy had a lower bleeding rate than hot snaring polypectomy, but the difference did not reach statistical significance [20]. Horiuchi et al. demonstrated that cold snaring polypectomy was associated with a significantly lower risk of immediate and delayed bleeding compared with hot snaring among patients who were taking an anticoagulant [15]. Because of their limited sample sizes and based on the lower risk of bleeding among high-risk individuals, the previous RCTs failed to demonstrate a reduced risk of bleeding in the group that underwent cold snaring polypectomy.

In this context, an RCT with a larger sample size is warranted to compare the risk of delayed bleeding between patients treated with cold versus hot snaring polypectomy techniques.

## Methods and design

### Study design

This trial is a prospective RCT comparing the risk of delayed bleeding following cold and hot snaring polypectomy for the treatment of small and diminutive colorectal polyps. This is a multicenter trial that will be conducted at National Taiwan University Hospital, Tri-Service General Hospital, Fu-Jen Catholic University Hospital, National Taiwan University Hospital, Hsin-Chu Branch, Chia-Yi Christian Hospital, and E-Da Hospital, all in Taiwan. These sites are located in the northern, central, and southern areas of Taiwan; it can provide adequate generalizability to represent the current clinical practice environment in Taiwan. The study was approved by the Institutional Review Board of the National Taiwan University Hospital (No. 201707022RINB) and it has also been registered at Clinical Trials.gov (NCT03373136). This trial protocol was written in accordance with the Standard Protocol Items: Recommendations for Interventional Trials (SPIRIT). The SPIRIT checklist has been included as Additional file 1.

### Study patients

Patients scheduled for screening or surveillance colonoscopy will be prospectively screened for eligibility and 4258 patients will be enrolled during the study period. The workflow is shown in Fig. 1. The inclusion criteria are as follows: patients aged > 20 years; have an indication for colonoscopy; and have at least one colorectal polyp of 4–10 mm in diameter. Patients who fulfill at least one of the following exclusion criteria will be considered ineligible for this study: (1) age < 20 years; (2) any contraindication for colonoscopy or polypectomy; (3) pregnancy; or (4) inadequate bowel preparation that could interfere with the procedure or polypectomy. The patients will be enrolled into this trial and provide informed consent at outpatient clinic visiting; they will have enough time to consider whether to participate in this study. The patients’ enrollment will not be the same day of the colonoscopy procedure. In addition, the management of antithrombotic agents for enrolled patients will follow the updated American Society for Gastrointestinal Endoscopy (ASGE) guideline [21]. Patients who fulfill the inclusion criterion will be randomized into either cold or hot snaring polypectomy treatment groups.

**Fig. 1 Fig1:**
[figure not shown]
Study workflow. Patients will be enrolled and will sign the inform consent in the outpatient department. The colonoscopy will be performed in the endoscopy unit. Patients who have colorectal polyps sized 4–10 mm will be randomized into either cold or hot snaring polypectomy regardless of whether large colorectal polyps are present. Small-sized polyps will be removed by hot or cold snaring polypectomy, depending on the the patient’s allocation to the cold or hot snaring group, and large-sized polyps (> 10 mm) will receive hot snaring polypectomy, EMR, or ESD according to the colonoscopist’s decision

### Endoscopists and equipment

Each procedure will be performed at the six study sites by one of the 17 endoscopists; each one collectively has experience with > 5000 colonoscopies.

Colonoscopes with a variable-stiffness function (CF-260 or 290 series; Olympus Medical Systems, Tokyo, Japan) will be used for all procedures. The following models of snare will be used for both cold and hot snaring polypectomy: Captivator-Small Hex 13 mm; Captivator II-Round 10 mm; and Captivator II-Round 15 mm (Boston Scientific, Boston, MA, USA). One of these snares will be applied for polypectomy of small polyps, depending on the size and morphology of the polyp and the preference of the endoscopists. Concurrent lesions > 10 mm will also be resected using snares other than the models just mentioned, depending also on the lesions’ size and morphology.

### Randomization

Randomization will be based on the appearance of the target lesions, polyps sized 4–10 mm, present at colonoscopy. Eligible patients will be centrally randomized 1:1 into either cold or hot snaring polypectomy by online software. The online software will be a web-based computer program accessed via an application on a smartphone (Interrand Inc., Ottawa, ON, Canada). Randomization procedures will be conducted by research assistants in the endoscopy units. The patients will be blinded about which treatment group they are randomized into during and after the procedures.

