### Procedures

For both groups, the procedures for bowel preparation and colonoscopy insertion will take place as described in a previous study [22]. Colorectal polyps sized < 4 mm will be removed by forceps biopsy. Lesions sized 4–10 mm will be removed either by hot or cold snaring polypectomy based on the allocation arm. No matter hot or cold snaring polypectomy, saline or adrenaline solution injection to the lesion will not be performed before polypectomy. Lesions sized ≥ 10 mm will be removed by hot snaring polypectomy, endoscopic mucosal resection (EMR), or endoscopic submucosal dissection (ESD) as indicated and based on the feasibility, risk, and patients’ consent. Patients who are allocated to the cold snaring group will receive snaring polypectomy without electrocautery for all target lesions except for lesions > 10 mm, for which hot procedures (polypectomy, EMR, or ESD) will be applied.

Image-enhanced endoscopy with either narrow band imaging or chromoendoscopy with 0.4% indigo carmine spraying will be applied in both arms before polypectomy, to confirm the diagnosis, and after polypectomy, to optically evaluate the complete eradication [23]. The total procedure time, the insertion time, the time to withdrawal, and the time required for polypectomy will be recorded.

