### Pathologic examination

All resected specimens will be sent to a central, dedicated pathologist for assessment of complete histologic eradication at all study hospitals. The pathologist will be a gastrointestinal specialist who will be blinded to the clinical information, including randomization. The diagnosis of adenomatous lesions will be based on the 2010 World Health Organization classification of tumors [24].

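### Lesions found or sized after allocation are classified by an endoscopist who knows the arm, so borderline sizing can differ by arm and can dilute the contrast

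*Protocol article*

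**What the plan says.** The Randomization section of the protocol article states: "Randomization will be based on the appearance of the target lesions, polyps sized 4–10 mm, present at colonoscopy". It adds: "Randomization procedures will be conducted by research assistants in the endoscopy units". Allocation is thus made in the endoscopy unit, during the procedure.

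Two parties are said to be blinded. For the patients: "The patients will be blinded about which treatment group they are randomized into during and after the procedures". For the reader of the specimens (Pathologic examination): "The pathologist will be a gastrointestinal specialist who will be blinded to the clinical information, including randomization". No blinding of the endoscopist is stated, and none would be possible, since the endoscopist carries out the allocated technique.

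The Procedures section lets size decide whether the allocation applies:
- Below the range: "Colorectal polyps sized < 4 mm will be removed by forceps biopsy".
- In the range: "Lesions sized 4–10 mm will be removed either by hot or cold snaring polypectomy based on the allocation arm".
- Above the range, in the cold arm: "Patients who are allocated to the cold snaring group will receive snaring polypectomy without electrocautery for all target lesions except for lesions > 10 mm". Hot procedures are used there instead.

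The Fig. 2 caption adds flat or sessile morphology to the definition of a target lesion. The Fig. 1 caption says that patients are randomised whether or not they also have large polyps.

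**The concern.** Size is a visual judgement, and two cut-offs (4 mm and 10 mm) decide whether a lesion gets the randomised technique. For lesions sized before allocation, that judgement cannot depend on the arm. For lesions found or sized afterwards it can, because the person judging knows the arm. An operator hesitant about cold-snaring a lesion near the upper limit may, without any intent to deviate, see it as just over the limit. A lesion near the lower limit may likewise be seen as small enough for forceps.

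Two things are at stake:

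1. **Delayed bleeding.** Cold-arm lesions moved to hot procedures bring the cold arm's risk closer to the hot arm's. The trial expects few events, so a modest shift costs visible power.
2. **Lesion-level secondary outcomes.** If eradication, tissue retrieval and polypectomy time are summarised over 4–10 mm lesions, membership of that set is partly decided after randomisation by someone who knows the arm. Randomising patients does not protect a comparison of lesions selected in this way.

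**Working it through.** **Step 1: does the mechanism follow from the text?**

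| Element | Where | What it gives |
|---|---|---|
| Trigger for allocation | Randomization | A 4–10 mm lesion appearing at colonoscopy |
| Who is blinded | Randomization; Pathologic examination | Patients and pathologist only |
| Rule for technique | Procedures; Fig. 1 caption | Judged size, with cut-offs at 4 mm and 10 mm |
| Further criterion | Fig. 2 caption | Flat or sessile morphology |
| Effect of a large lesion on eligibility | Fig. 1 caption | None |

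The pathologist's blinding does not help here, because the specimen arrives after the technique has been chosen. Nothing in the article fixes lesion sizes before the arm is revealed.

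**Step 2: reproduce the plan's sample size.** Inputs from Sample size calculation and statistical analysis: hot-arm risk p1 = 0.006; reduction 77%, so cold-arm risk p2 = 0.006 × 0.23 = 0.00138; power 80%; significance level 0.05.

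n per arm = [z_α √(2p̄(1−p̄)) + z_β √(p1(1−p1) + p2(1−p2))]² / (p1 − p2)², with p̄ = (p1 + p2)/2 = 0.00369.

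- One-sided 0.05: [1.645 × 0.08575 + 0.8416 × 0.08569]² / 0.00462² = 2129 per arm, total 4258. This is the plan's figure.
- Two-sided 0.05 (z = 1.960): 2703 per arm, total 5406. At 2129 per arm, two-sided power is 70%.

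The article does not state sidedness, so both scales are carried forward. Expected events are 2129 × 0.006 ≈ 12.8 hot and 2129 × 0.00138 ≈ 2.9 cold.

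**Step 3: dilution.** Let f be the share of cold-arm risk that reverts to hot risk. The document gives no value, so f is an assumption, shown from 5% to 20%.

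Cold-arm risk q = p2 + f(p1 − p2) = 0.006 × (0.23 + 0.77f).

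Power = Φ{[(p1 − q)√2129 − z_α √(2p̄(1−p̄))] / √(p1(1−p1) + q(1−q))}, with p̄ now (p1 + q)/2.

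| f | Cold-arm risk | Risk ratio | Power, one-sided | Power, two-sided |
|---|---|---|---|---|
| 0 | 0.138% | 0.23 | 80% | 70% |
| 5% | 0.161% | 0.27 | 75% | 64% |
| 10% | 0.184% | 0.31 | 70% | 58% |
| 20% | 0.230% | 0.38 | 59% | 47% |

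To restore 80% power at f = 10% would take 5586 patients one-sided or 7090 two-sided. The loss is similar on either scale, so the point does not depend on how sidedness is settled.

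**Step 4: lesion-level outcomes.** No figure can be derived. Eradication, retrieval and polypectomy time depend on which lesions are counted, and the article gives neither the share of borderline lesions nor the share found after allocation.

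**The case against.** Several counter-arguments carry weight.

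- **Timing is not spelled out.** The wording on the appearance of lesions could also fit allocation after the bowel has been inspected, and the workflow figure is not shown. Allocation once a lesion appears is the natural reading, but not a stated fact. Even under the other reading, nothing stated fixes sizes before the arm is known.
- **Deliberate mis-sizing would breach the protocol.** Procedures requires 4–10 mm lesions to be removed by the allocated technique. A reader might infer that an operator could relabel lesions and still comply. The text does not support that, and nothing suggests that these operators, each with more than 5000 colonoscopies, would do so. What remains is honest judgement at the margin, which experience does not blind.
- **Not every reclassification narrows the contrast.** A hot-arm lesion judged too large still gets a hot procedure. Movement to forceps at the lower limit has an unclear effect, because the Background says forceps biopsy can be hot or cold.
- **f has no support in the document.** Every randomised patient has at least one lesion judged eligible before allocation, so f arises only from further, borderline lesions. The upper part of the range may be pessimistic.
- **Condensed reporting.** Form fields and lesion analysis sets often sit in the full protocol or analysis plan, so their absence here is not the criticism. The point rests on the stated trigger, the stated blinding and the stated size rule.

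A reader might also infer that the secondary outcomes are biased towards cold snaring. The document does not fix that. All resected specimens go to the pathologist, and eradication is not expressly restricted to target lesions.

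**Conclusion.** The concern holds as a risk that the stated design leaves open, not as a demonstrated bias. It rests on the natural reading that allocation occurs once an eligible lesion appears, and on an unblinded operator judging the size and morphology of further lesions.

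For delayed bleeding, the patient-level intention-to-treat comparison keeps its randomised groups. Upsizing in the cold arm would dilute the effect, not create a false benefit. Under the assumed 5–20%, the cost is about 5 to 21 percentage points of power one-sided (80% to 75–59%) or about 6 to 23 two-sided (70% to 64–47%).

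For eradication, retrieval and polypectomy time, the 4–10 mm lesion set can become arm-dependent, with unknown direction and size.

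This is a worthwhile, inexpensive improvement. It does not invalidate the primary analysis. The overlap at exactly 10 mm in Procedures, where two rules cover the same lesion, is a separate point to be reconciled. Settling it would leave judgement at both cut-offs.

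**What to change.** 1. Before the research assistant opens the randomisation app, enter the size and site of every 4–10 mm lesion seen so far and flag these as index lesions.
2. Record the size of each later lesion before it is removed.
3. State that all lesions are analysed by allocated arm, whatever technique was used. For the lesion-level outcomes, prespecify a sensitivity analysis restricted to index lesions.
4. Report by arm the number of lesions per patient classed < 4 mm and > 10 mm after allocation. An imbalance would be a direct sign of arm-dependent sizing.

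A sentence in Randomization should also say when allocation takes place relative to inspection of the remaining bowel.

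Cost: a few form fields, seconds per patient, and lower precision in the index-lesion analysis. No treatment rule changes. Pre-allocation sizes cannot be recovered later. Trial status describes the trial as still in preparation, so the fields should be in place before the first patient is randomised.

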### Procedures

For both groups, the procedures for bowel preparation and colonoscopy insertion will take place as described in a previous study [22]. Colorectal polyps sized < 4 mm will be removed by forceps biopsy. Lesions sized 4–10 mm will be removed either by hot or cold snaring polypectomy based on the allocation arm. No matter hot or cold snaring polypectomy, saline or adrenaline solution injection to the lesion will not be performed before polypectomy. Lesions sized ≥ 10 mm will be removed by hot snaring polypectomy, endoscopic mucosal resection (EMR), or endoscopic submucosal dissection (ESD) as indicated and based on the feasibility, risk, and patients’ consent. Patients who are allocated to the cold snaring group will receive snaring polypectomy without electrocautery for all target lesions except for lesions > 10 mm, for which hot procedures (polypectomy, EMR, or ESD) will be applied.

Image-enhanced endoscopy with either narrow band imaging or chromoendoscopy with 0.4% indigo carmine spraying will be applied in both arms before polypectomy, to confirm the diagnosis, and after polypectomy, to optically evaluate the complete eradication [23]. The total procedure time, the insertion time, the time to withdrawal, and the time required for polypectomy will be recorded.

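### Procedures gives two conflicting treatment rules for a lesion of exactly 10 mm; the ≥ sign should be >

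*Protocol article*

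**What the plan says.** The Procedures section sets resection technique by lesion size. For the target range the rule is "Lesions sized 4–10 mm will be removed either by hot or cold snaring polypectomy based on the allocation arm". After a sentence on submucosal injection comes the rule for larger lesions: "Lesions sized ≥ 10 mm will be removed by hot snaring polypectomy, endoscopic mucosal resection (EMR), or endoscopic submucosal dissection (ESD) as indicated". The next sentence concerns the cold arm alone and asks for snaring without electrocautery "for all target lesions except for lesions > 10 mm, for which hot procedures (polypectomy, EMR, or ESD) will be applied".

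The cut-off for large lesions also appears in two other places:

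- Fig. 1 caption: "Small-sized polyps will be removed by hot or cold snaring polypectomy, depending on the" allocation, while "large-sized polyps (> 10 mm) will receive hot snaring polypectomy, EMR, or ESD". Patients are randomised "regardless of whether large colorectal polyps are present".
- Endoscopists and equipment: "Concurrent lesions > 10 mm will also be resected using snares other than the models just mentioned".

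The target range is given as 4 to 10 mm in the eligibility criteria (Study patients), in the Fig. 2 caption and in the Randomization section: "Randomization will be based on the appearance of the target lesions, polyps sized 4–10 mm, present at colonoscopy".

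**The concern.** A lesion measured at 10 mm lies inside the target range and also satisfies the ≥ 10 mm rule, so two instructions apply to it. This size threshold decides which lesions receive the randomised technique, and 17 endoscopists at six sites will apply it.

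The consequences differ by arm:

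- **Cold arm.** The allocation rule requires cold snaring and the ≥ rule requires a hot procedure. They are incompatible. A patient whose only eligible polyp is 10 mm would be randomised to cold snaring, treated hot, and still analysed as cold under intention to treat. That pulls the arms together.
- **Hot arm.** Hot snaring satisfies both rules, so nothing need be violated. The ≥ rule does, however, permit EMR or ESD on a target lesion, which is not the comparator the trial describes. The article gives no bleeding risk for those techniques, so the direction of any effect on the hot-arm rate is unknown.

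The planned event counts are small: 2129 × 0.006 = 12.8 in the hot arm and 2129 × 0.00138 = 2.9 in the cold arm. Avoidable dilution is therefore unwelcome even when slight.

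**Working it through.** **Step 1. Compare every statement of the boundary.**

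| Place in the article | Rule | Where 10 mm goes |
|---|---|---|
| Study patients (eligibility) | 4–10 mm | target lesion |
| Randomization | 4–10 mm | target lesion |
| Fig. 2 caption | 4–10 mm | target lesion |
| Procedures, allocation sentence | 4–10 mm | allocated technique |
| Procedures, cold-arm sentence | exception only if > 10 mm | cold snare |
| Fig. 1 caption | large means > 10 mm | allocated technique |
| Endoscopists and equipment | concurrent lesions > 10 mm | not a large lesion |
| Procedures, large-lesion sentence | ≥ 10 mm | hot snare, EMR or ESD |

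The large-lesion cut-off is stated four times: three times as > 10 mm and once as ≥ 10 mm. The < 10 mm in the Abstract and Background describes earlier studies and screening-detected polyps and is not a rule of this trial. Both signs print correctly elsewhere in the article, so there is no reason to suspect a text-conversion error.

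**Step 2. Reproduce the planned sample size.** Inputs from the sample size section: hot-arm risk p₁ = 0.006; 77% reduction, so p₂ = 0.006 × (1 − 0.77) = 0.00138; power 80%; significance level 0.05, sidedness not stated. The pooled-variance formula without continuity correction, with p̄ = (p₁ + p₂)/2, is

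n = [z_α √(2p̄(1 − p̄)) + z_β √(p₁(1 − p₁) + p₂(1 − p₂))]² / (p₁ − p₂)².

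A one-sided 0.05 test gives 2129 per arm (4258 in total), which is the stated figure. A two-sided 0.05 test gives 2703 per arm. Power is therefore shown below on both bases; the 10 mm point does not depend on which is meant.

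**Step 3. Illustrate the dilution.** Assume that a share s of cold-arm patients carries the hot-snare risk because a 10 mm target lesion was treated hot:

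p₂(s) = 0.00138(1 − s) + 0.006s,

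power = Φ{[(p₁ − p₂(s))√n − z_α √(2p̄(1 − p̄))] / √(p₁(1 − p₁) + p₂(s)(1 − p₂(s)))}, with n = 2129 and p̄ recalculated for each s.

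| Assumed s | Cold-arm patients | p₂(s) | Expected cold-arm events | Power, one-sided 0.05 | Power, two-sided 0.05 |
|---|---|---|---|---|---|
| 0% | 0 | 0.1380% | 2.94 | 80.0% | 70.1% |
| 1% | 21 | 0.1426% | 3.04 | 79.1% | 68.9% |
| 2% | 43 | 0.1472% | 3.13 | 78.1% | 67.8% |
| 5% | 106 | 0.1611% | 3.43 | 75.2% | 64.3% |
| 10% | 213 | 0.1842% | 3.92 | 70.1% | 58.4% |

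The losses at 1% and 2% are 0.9 and 1.9 points one-sided, and 1.1 and 2.3 points two-sided. The article gives no value for s. The larger shares would need many patients with a 10 mm polyp and sites that consistently preferred the ≥ sentence to the one after it. Use of EMR or ESD in the hot arm is not modelled, because the article gives no risk for it.

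**The case against.** The best defence is that the article resolves the conflict itself. The sentence straight after the ≥ rule is specific to the cold arm, which is the only arm in outright conflict, and it exempts only lesions above 10 mm from cold snaring. The Fig. 1 caption agrees. A reader who finishes the paragraph should treat a 10 mm lesion cold. The design also already accepts hot procedures in cold-arm patients who have concurrent lesions above 10 mm. The power figures rest on assumed shares and show no actual harm.

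Most of this stands. The intended rule is recoverable, the affected lesions are those measured at exactly 10 mm, and the illustration should not be used to raise the severity. Two things remain. The cold-arm sentence does nothing for the hot arm, where the text still permits EMR or ESD on a 10 mm target lesion. And allowing hot removal of a concurrent large lesion is different from directing hot removal of the lesion that triggered randomisation. Nor is this a detail that an article may leave to a fuller document: the article states two rules and they disagree.

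**Conclusion.** The inconsistency is real and the concern holds as a minor one. As written, a 10 mm target lesion falls under two treatment rules, incompatible in the cold arm and looser than intended in the hot arm. The rest of the article shows that 10 mm should follow the allocation. The practical effect is probably small but cannot be bounded from the article, which gives neither the share of patients with a 10 mm lesion nor the bleeding risk of such lesions or of EMR and ESD. At assumed shares of 1% to 2% of cold-arm patients the power loss is about 1 to 2 points, and it grows with the share. The conclusion rests on the wording alone, not on those figures.

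**What to change.** In the large-lesion sentence of Procedures, replace ≥ 10 mm with > 10 mm. A 10 mm lesion then follows the allocated snare technique in both arms, and EMR or ESD is reserved for lesions above 10 mm. No other sentence needs to change. The cost is one symbol, corrected before the planned July 2018 launch; sample size, endpoint and analysis stay as they are.
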